For both jails, sample size calculations are made comparing the uptake at intake compared to subsequent timepoints. While, for the purposes of this pilot study, we do have three arms to have a more complete programmatic experience, the most relevant analysis is to just compare intake with post-intake. Since we are randomizing 1:1:1, this results in a 2:1 comparison for the primary outcome comparing the intake group with the collapsed post-intake groups. Table 1 provides sample size estimates for each arm, based on using the chi-square tests to compare the proportion uptake at each time-point within each jail setting and calculated using the standard sample size formula:

Where p is the proportion who receive an HIV test at intake, alpha is the type 1 error rate, beta is the type 2 error rate, and delta is the difference between the intake and post-intake groups. Plausible ranges of uptake rates are garnered from our current experiences in the jail system, through extensive clinical interviews and discussions with jail counselors. Only one other study has assessed routine testing in a jail setting. That study, however, is likely to have significantly higher uptake rates than will be seen in our study, since many of the subjects were repeat testers and the program had been running in that jail for some time.23

At our best-estimated initial uptake of 60% for men and 75% for women, 100 subjects in each arm will detect differences of 16% and 13%, respectively, with a type 1 error rate of 0.05 and power of 80%.

| **Table 1. Sample Size Calculations** | | |  |  |
| --- | --- | --- | --- | --- |
| **Jail Setting** | **Intake** | **Subsequent Time-points** | **N (each arm)** | **3N (Total Subjects)** |
| Men | 50% | 65% | 126 | 378 |
| 55% | 70% | 121 | 363 |
| **60%** | **76%** | **98** | **294** |
| 65% | 80% | 101 | 303 |
| 70% | 84% | 103 | 309 |
| Women | 65% | 80% | 101 | 303 |
| 70% | 84% | 103 | 309 |
| **75%** | **88%** | **100** | **300** |
| 80% | 92% | 93 | 279 |
| 85% | 95% | 99 | 297 |

3.A.5 Procedures

3.A.5.1 Testing

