## Section VIII: Protection of Research Subjects

1. **Risks:** What are the reasonably foreseeable risks, discomforts, or inconveniences associated with participation in the research?

The risks in this study are minimal – potential risks could however include breaches of confidentiality within the jail. If jail guards or other inmates were to learn of an individual’s HIV status, it could lead to discriminatory behavior and even physical harm. In addition, learning of one’s own HIV status could be both upsetting news and potentially difficult information for inmates to deal with constructively, especially within the often chaotic correctional setting. Lastly, it is possible that with the high turnover in the jail setting, an inmate might test preliminarily positive using the OraQuick rapid HIV test but will be released before a confirmatory result can be delivered.

The published sensitivity and specificity for the OraQuick Advance Rapid HIV-1/2 Antibody oral test are 99.3% (95% confidence interval [CI] = 98.4% -- 99.7%) and 99.8% (CI = 99.6% -- 99.9%). According to these reported rates, it would be expected that for every 1000 individuals tested, 2 would receive false positive results.

Our research protocol proposes to test 600 individuals. Therefore, while it is still possible for one of our subjects to falsely test positive, the likelihood is very small.

Please note: Potential research risks include more than physical harm; risks may also include, for example, emotional or psychological harm, risk of social stigmatization, economic or legal risk.

1. **Minimizing Risks:** How will the above-mentioned risks be minimized?

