All inmates who test preliminarily positive will receive post-test counseling from trained DOC HIV testing counselors. Any inmate who describes suicidal ideation, or any other acute medical or psychiatric condition, will be immediately referred to the prison health staff for professional assessment. Preliminarily positive patients will then undergo confirmatory testing with either a Western blot or immunofluorescent assay (IFA) for confirmation of test results. Actual consent for participation in this study will be obtained only by study personnel listed on our protocol. No CMHC or DOC personnel will be consenting subjects to participate in this study. All testing and delivery of preliminary positive results will be conducted by these trained counselors in coordination with study staff using existing medical facilities within the jail setting and will be documented appropriately in accordance with DOC confidentiality protections.

Among those inmates who receive HIV testing, the incidence of HIV is estimated to be approximately 2% in correctional settings in the United States. According to Connecticut law, all inmates testing positive for HIV infection are entitled to treatment within the correctional setting. Under these guidelines, the DOC will be expected to pay for treatment of all subjects identified as HIV positive. Administrators from Connecticut Correctional Managed Healthcare (CMHC) have expressed their willingness to participate in this study and are aware of their obligation to treat subjects identified as HIV positive.

Continuity of care is provided for all HIV-positive inmates housed in the Connecticut correctional system through Project TLC (Transitional Linkage to Care).  Project TLC was created by the PI for this protocol and has been in place in the Connecticut Department of Corrections since 1997.  Prior to release, every HIV positive-inmate will meet with a case manager who will conduct a needs assessment for the inmate.  The needs assessment includes:

- a two weeks discharge supply of free antiretroviral medications and other medications the inmate is currently taking

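### The risk section calls a false positive among 600 tested very unlikely, but its own specificity figure implies about one (probability of at least one about 69%)

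*Protocol*

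**What the plan says.** In the protocol, Section VIII, the Risks item gives the oral rapid test a published specificity of 99.8%, with a 95% confidence interval of 99.6% to 99.9%. From this it states that "it would be expected that for every 1000 individuals tested, 2 would receive false positive results". The next paragraph says "Our research protocol proposes to test 600 individuals" and then, introduced by the word therefore, that "while it is still possible for one of our subjects to falsely test positive, the likelihood is very small".

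Other statements that bear on the point:

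- Section VIII, Minimizing Risks, on those who receive testing: "the incidence of HIV is estimated to be approximately 2% in correctional settings in the United States". The protocol says incidence; I read it as the proportion infected among those tested.
- Section III (Number of Subjects) and Section VI (Subject Population) give 600 as the number to be recruited. Section IV, 3.A.4, plans on less than full uptake.
- Section IV, 3.A.5.2, has preliminary positive results delivered the same evening (Day 1 and Day 7 groups) or the next morning (Day 0 group). Under Minimizing Risks, confirmatory testing follows counselling.
- The Risks item also warns that an inmate who tests preliminarily positive "will be released before a confirmatory result can be delivered".

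**The concern.** The paragraph moves from a rate of 2 per 1000 to a planned 600 tests and concludes that a false positive is improbable. Scaling the rate to 600 gives more than one expected event, so the conclusion does not follow from its premises.

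The sentence is part of the answer to the review committee's question about reasonably foreseeable risks, in a study population made up entirely of prisoners. A false preliminary positive reaches the inmate before any confirmatory result. The protocol itself says that such news can be upsetting and hard to handle in jail. A committee relying on the sentence would treat as remote an event that the quoted data make roughly the expected outcome.

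**Working it through.** **Inputs**

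- Specificity 99.8%, interval 99.6% to 99.9% (Section VIII, Risks). The false-positive rate per uninfected person tested is therefore 0.2%, range 0.1% to 0.4%.
- Number tested: 600, as that item states.
- Proportion infected: about 2% (Section VIII, Minimizing Risks), so 600 × 0.98 = 588 uninfected.

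**The protocol's own figure.** 1000 × 0.002 = 2.0, or 980 × 0.002 = 1.96 with 2% infected. The stated 2 per 1000 is reproduced.

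**Scaled to 600.** Expected false positives = uninfected × (1 − specificity). This is 588 × 0.002 = 1.18, or 600 × 0.002 = 1.20 if nobody is infected.

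**Probability of at least one** = 1 − specificity^(number uninfected):

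| Specificity | Expected, 588 uninfected | P(at least one) |
|---|---|---|
| 99.9% | 0.59 | 44% |
| 99.8% | 1.18 | 69% |
| 99.6% | 2.35 | 91% |

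With all 600 uninfected, the value at 99.8% is 70%. The probability of two or more at 99.8% is about 33%.

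**If fewer are tested.** Table 1 of 3.A.4 has best-estimate uptake of 60% at intake and 76% later for men, and 75% and 88% for women. With 100 per arm in each jail:

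- Men: 100 × 0.60 + 200 × 0.76 = 212.
- Women: 100 × 0.75 + 200 × 0.88 = 251.
- Total: 463 tested, of whom about 454 are uninfected at 2%.

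Expected false positives are 454 × 0.002 = 0.91. The probability of at least one is 1 − 0.998^454 = 60%, or 37% at 99.9% specificity and 84% at 99.6%. The count of 463 is an assumption, since it carries the planning rates straight over to numbers tested.

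**Where one half is crossed.** At 99.8%, ln 0.5 / ln 0.998 = 346.2. The probability therefore stays above 50% as long as at least 347 uninfected people are tested.

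**Share of preliminary positives that are false**, using the quoted sensitivity of 99.3%. The predictive value is 0.993π / (0.993π + 0.002(1 − π)), where π is the proportion infected.

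- π = 2%: 0.910, so about 1 in 11 is false.
- π = 1.1% (the positivity that the Background reports for the jail demonstration projects): 0.847, so about 1 in 6 to 7 is false.

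**The case against.** **The per-person reading.** The form asks about the risks of participation, and for one uninfected person the chance of a false positive is 0.2%, which is fairly called small. The 2 per 1000 figure is also disclosed just before, so the committee could scale it. The disclosure stands to the protocol's credit, but the reading does not rescue the sentence: the conclusion is drawn from the 600 to be tested and speaks of one among the subjects, so it is a study-level claim.

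**Confirmatory testing.** Every preliminary positive is to be counselled and confirmed, and only confirmed results go to the state. That corrects a false result but does not prevent it, because the preliminary result is given to the inmate first.

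**Dependence on the point estimate and on 600.** This stands in part. That a false positive is more likely than not holds at 99.8% but not at 99.9%. The number tested is also uncertain. Opt-outs, incompetence and release lower it, while re-invitation of Day 0 and Day 1 inmates raises it, and the Table 1 rates may already allow for release. So 463 is an illustration, and going lower by removing further Day 7 losses would risk counting release twice.

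**Stronger readings that a reader might infer.**

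- That prisoners are misinformed in the consent form. The form is attached to the protocol but was not available for this review, so this cannot be said.
- That 1 in 11 preliminary positives will be false. This holds only at 2% infected; the Background gives 1.1% in one setting and suggests several-fold more than 1% in Northeast jails.
- That the protocol overlooks release before confirmation. It names that risk in the paragraph before the specificity figures, and whether to tie the two together is a drafting preference. The 72-hour release figure in 3.A.7 counts from jail entry, so it cannot be applied to inmates tested on Day 7.

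**Conclusion.** The statement is wrong as written. On the protocol's own specificity, 600 tested and about 2% infected, about 1.2 false preliminary positives are expected and the probability of at least one is about 69%. The range is about 44% to 91% over the quoted specificity interval. With about 463 tested (assumed) it is about 60%, range about 37% to 84%. None of these values is very small, so the conclusion does not depend on the exact specificity within that interval or on choosing between these two counts.

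The calculation treats tests as independent with a common specificity and takes 2% as the infected proportion. The last hardly matters here: assuming nobody infected moves 69% only to 70%.

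This is an error in the risk description and should be corrected. It is not a design flaw, and the primary outcome, its analysis and the sample size do not depend on it.

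**What to change.** In Section VIII, Risks, replace the sentence with wording such as:

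> The risk to any one uninfected person tested is about 0.2%, but if 600 are tested about one false preliminary positive is expected (probability of at least one about 69%, range about 44% to 91% over the specificity interval; somewhat lower if fewer are tested).

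In the same place, note that 600 is the number to be recruited and that the number actually tested may be lower.

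If a predictive value is added, say that it depends on prevalence and give more than one value: about 1 in 11 preliminary positives false at an assumed 2%, and about 1 in 6 to 7 at 1.1%.

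The sponsor should check whether the consent form repeats the statement and, if so, align it.

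The cost is one or two sentences and a less favourable stated risk. No procedure, sample size or analysis changes.

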1. Inmates who arrive on each intake night (Monday through Friday) will be assigned to be offered testing and approached for participation in the study at one of three time points based on the total number of inmates proceeding through intake that night and their arrival times to the jail. One third of inmates will be assigned to be approached for routine HIV testing and study participation the night of intake itself during routine health screening and mental health assessment (9pm – 1am). One third of inmates will be assigned to be approached for routine HIV testing and study participation the evening following intake when all arriving inmates undergo a routine physical exam. The final third of inmates will be assigned to be approached for routine HIV testing and study participation seven days after arriving at the facility.
2. Depending on the testing group to which the inmate is assigned (Day 0, Day 1, or Day 7 – see figure below), either the intake nurse, the physician’s assistant performing physical exams, or a member of the research study staff will offer to swab the inmate for HIV testing. It will be explained that HIV testing is now done using an oral swab and that results can be made available within a short period of time. Individuals offered testing on Day 0 (intake night) will be told that they will receive their results the following morning. Individuals tested on Day 1 and Day 7 will be told they will receive their results that afternoon/evening. The inmate will be instructed that HIV testing, like many other conditions, can be performed as part of routine screening in the jail setting, similar to other medical conditions such as substance abuse urine testing, and screening for tuberculosis, pregnancy (for women) and hypertension.
3. At this point, the inmate will be given an opportunity to opt-out of being swabbed for testing. If the inmate opts out and is part of the Day 0 or Day 1 testing group, s/he will be invited back for testing on Day 1 or Day 7, respectively. If the inmate is part of the Day 7 testing group, s/he will not be approached again for testing.
4. If the inmate agrees to be swabbed, the inmate will meet with a member of the research study staff who will ask the subject to provide 2 separate written consents – one to participate in the study, and one to have the swab tested for HIV. Only research staff will be obtaining consent for this study.

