The study staff and HIV counselors at both sites include individuals who are bilingual/bicultural in Spanish and English. A Spanish consent form has been submitted for approval. No mono-lingual Spanish speakers will be enrolled until final HIC approval of the Spanish consent form.

- 1. **Parental Permission and Assent:** For research involving minors, please explain how parental permission and child assent will be obtained.

Not applicable

- 1. **Documentation of Consent:** Specify the forms that will be used among the following: adult consent form, parental permission form, LAR (Legally Authorized Representative) permission form, adult assent form, adolescent assent form (ages 13-17 inclusive), child assent form (ages 7-12 inclusive), and information sheet. Copies of all forms should be appended to the protocol, in the same format that they will be given to subjects.

Attached

- 1. **Waiver of Consent:** Will you request either a waiver of consent, or a waiver of signed consent, for this study? If so, please address the following:

We do not request a waiver of consent or a waiver of signed consent for this study.

*Waiver of consent*:

- 1. Does the research pose greater than minimal risk to subjects?
  2. Will the waiver adversely affect subjects’ rights and welfare?
  3. Why would the research be impracticable without the waiver?
  4. How will pertinent information be returned to subjects, if appropriate at a later date?

*Waiver of signed consent*:

1. Does the research pose greater than minimal risk? If so, does a breach of confidentiality constitute the principal risk to subjects?
2. Would the signed consent form be the only record linking the subject and the research?
3. Does the research include any activities that would require signed consent in a non-research context?
   1. **HIPAA Authorization:** If the research involves the creation, use or disclosure of PHI, separate authorization is required under the HIPAA Privacy Rule. Please provide the HIPAA Research Authorization Form and/or a request for waiver of HIPAA authorization. *(For further information, see the Yale HIPAA website at* <http://info.med.yale.edu/hipaa/>).

Attached.

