Potential instances for breaches of confidentiality include during the interview process or during delivery of positive test results. From our research efforts and provision of clinical care for inmates within the correctional system, we have paid careful attention to potential breaches of confidentiality for subjects undergoing interviews. [name], the Principal Investigator, has written extensively on the legal and ethical issues with regard to conducting clinical trials among prisoners.30,31 All interviews will be conducted individually during the second shift when rooms are more accessible for consent procedures and privacy can be ensured. Rooms are private and the information collected from individual interviews will be confidential. Appointments will be staggered to avoid participant encounters in the interview room or in the outside hallway. All information will be stored in password-protected computers with double-password protection for opening specified files. All confidential information (study instruments, HIV status, etc.) will be recorded with study participant number only and maintained in locked cabinets within our offices at the Yale University AIDS Program and will only be available to be opened by the Study Coordinator, study staff, or the Principal Investigator. Electronic databases will be maintained through password-protected computers and files and maintained on a single computer at the Yale University AIDS Program. No data will be stored on laptops, flash drives, or be transported via email or any other medium. The data will be stored according to a study ID number and therefore will contain no names, prison ID numbers, or any other personal identifiers. Identifying information will not be stored. All data will be encrypted using encryption software provided by Yale Information and Technology Services.

Study participants should not have to worry about being identified as HIV+ by participating in the study, since all newly entering inmates will be eligible, most of whom will not be HIV+. We have designed this study so that capacity is not so excessive that confidentiality is likely to be breached.

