   2. All confidential information (study instruments, test results, etc.) will be recorded with a study participant number only. This study participant number will be different from the participant’s prison ID number and will in no way serve as a personal identifier. A HIPAA Research Authorization form will be signed by all participants. Information collected will be maintained in locked cabinets within our offices at the Yale University AIDS Program, and will only be available to be opened by the Study Coordinator, study staff, or the Principal Investigator. No data will be stored on laptops, flash drives, or be transported via email or any other medium. The data will be stored according to a study ID number and therefore will contain no names, prison ID numbers, or any other personal identifiers. Identifying information will not be stored. All data will be encrypted using encryption software provided by Yale Information and Technology Services. In accordance with federal and university policy, all research personnel are compliant with HIPAA training. If any breach of data confidentiality were detected, we would use similarly detailed procedures for report to the PI and HIC simultaneously.
   3. How will research data be collected and recorded?

Research data will be collected via interview and via the carrying out of HIV testing after consent as described above.

In order for subjects to be invited back on subsequent days for interviews or for delivery of test results their names and prison ID number must be recorded. These names and prison ID numbers will be recorded on a sheet along with a unique study ID number for each subject. This will be the only record linking study number and subject identification. This sheet will be kept in a locked cabinet in the HIV testing counselor’s office at each study site. Only the HIV testing counselor and study personnel will have access to this sheet. At no time will this sheet leave the HIV testing counselor’s office.

The interview forms, informed consent documents, and the swabs used for the rapid HIV tests will be labeled only with the study ID number and no personal identifying information. After the study has been completed, the record of names and prison ID numbers linked to study ID numbers will be shredded and destroyed.

**Data Sources:** These will include: Structured interviews; HIV Testing Results; and Correctional Databases.

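### Signed consent forms labeled with the study ID are themselves name-to-ID links, so the name sheet is not the only link and shredding it alone does not break the connection

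*Protocol*

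**What the plan says.** Protocol Section VIII, under Confidentiality, sets up a coding scheme. A sheet holds each subject's name, inmate number and study ID, and is locked in the HIV testing counselor's office at each site. Of this sheet the protocol says: "This will be the only record linking study number and subject identification". The same item says that interview forms, "informed consent documents, and the swabs used for the rapid HIV tests will be labeled only with the study ID number", and that these items carry no personal identifiers. At study end, "the record of names and prison ID numbers linked to study ID numbers will be shredded and destroyed". Nothing is said there about where the signed consent forms are kept, for how long, or whether they are destroyed.

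Section IV, 3.A.5.1 (Testing), has research staff "ask the subject to provide 2 separate written consents", one for the study and one for testing the swab. Section VII repeats this under Process of Consent. Under Waiver of Consent it states: "We do not request a waiver of consent or a waiver of signed consent for this study".

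**The concern.** A consent form signed by the subject identifies that subject. If the same sheet of paper carries the study ID, anyone holding it can go from the signer to the ID, and from the ID to the interview form and the study's record of the HIV result. The protection described in Section VIII depends on there being one link, which is then destroyed. Followed as written, the labeling rule creates a further link for every inmate who consents.

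The setting makes this more than a matter of wording. Section VIII names breach of confidentiality first among the risks, Section VI treats all subjects as vulnerable, and Section VIII records that no Certificate of Confidentiality was obtained. The coded interviews cover withdrawal symptoms, suicidal ideation and psychological distress. The coding scheme is therefore a main protection for these data.

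**Working it through.** The protocol gives no figure to reproduce. The check is whether its statements can hold together, followed by a count of the forms involved.

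**Consistency**

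1. Consent is written and signed: two written consents per subject (Section IV, 3.A.5.1; Section VII, Process of Consent) and no waiver of signature (Section VII, Waiver of Consent).
2. Consent documents carry the study ID (Section VIII, Confidentiality).
3. From 1 and 2, each consent document carries a signature and the study ID. It therefore links person to ID.
4. Section VIII says the consent documents carry no personal identifiers. This conflicts with 1, because a signature is one.
5. Section VIII says the name sheet is the only linking record. This conflicts with 3.
6. Only the name sheet is listed for destruction. Under 3, a link remains for as long as the consent forms are kept.

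The protocol's own application template points the same way. Among its questions on waiving signed consent, it asks whether the signed form would be the sole record connecting subject and research. It thus treats a signed consent form as a possible linking record.

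**Number of forms**

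Inputs: about 600 subjects (Section III); two written consents each (Section IV, 3.A.5.1); about 100 subjects per arm and three arms per jail (Section IV, 3.A.4); planning uptake from the bolded rows of the sample size table, men 60% at intake and 76% later, women 75% and 88%.

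- Ceiling, if all 600 sign once: 600 × 2 = 1,200 forms.
- Men tested at planning uptake: 100 × 0.60 + 200 × 0.76 = 60 + 152 = 212.
- Women tested at planning uptake: 100 × 0.75 + 200 × 0.88 = 75 + 176 = 251.
- Total tested: 212 + 251 = 463, giving 463 × 2 = 926 forms.

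Inmates who sign and are then found incompetent add to the 926, because the competency tool is given after consent. The protocol gives no rate for them. Section VI says data on these inmates will not be kept, so their forms lead to little.

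**The case against.** The strongest reply is that this is loose wording. Labeling may mean only what staff write on the form, and the consent pages are not available, so a printed-name line cannot be confirmed. Section VII also says many inmates cannot read or write, so some signatures may be illegible or only a mark. This limits how easily a given form could be traced to a person. It does not rescue the claim that there is only one link, because the required signature on an ID-labeled form is enough to contradict it.

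Several stronger readings are tempting but are not supported:

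- **The HIPAA form as a further link.** The protocol says "A HIPAA Research Authorization form will be signed by all participants", but nowhere puts the study ID on that form. It does not count.
- **Links that certainly survive the study.** Retention of the consent forms is not stated. That they outlast the sheet is an inference from silence.
- **Greater danger inside the jail.** The in-jail risk in Section VIII is that guards or other inmates learn someone's HIV status. The place where consent forms are kept is not given, so exposure in the jail through them is not shown. HIV results also go to corrections medical records by design, so a named HIV record exists there regardless.
- **A flat contradiction of "Identifying information will not be stored".** In each place this sentence follows one about storing data by study ID and precedes one about encryption. It describes the research data and can be read as silent on consent paperwork.
- **1,200 as the expected count.** That is a ceiling, reached only if every inmate signs.

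**Conclusion.** The concern holds as an internal contradiction with a practical consequence. Signed consents, study-ID labels on them, the absence of personal identifiers, and a single linking record cannot all be true. As written, the labeling rule defeats the link-destruction safeguard for as long as the forms are kept.

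The number affected is two forms per consenting inmate: about 926 at planning uptake plus those later found incompetent, and at most 1,200 if each of 600 inmates signs once. What is newly exposed is mainly the interview answers and the study's own copy of the HIV result.

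The conclusion assumes that the signature identifies the signer and that the labeling rule is followed literally. It needs no printed name and no assumption about the HIPAA form. The primary outcome, sample size and analysis are untouched. The point should still be corrected, because it concerns a protection promised to vulnerable subjects and costs almost nothing to put right.

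**What to change.** In Section VIII, Confidentiality:

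1. Remove the consent documents from the list of items labeled with the study ID.
2. State that signed forms carry no study ID and are kept in a separate locked cabinet at the university offices, apart from coded data and not in the jail. Filing them with the name sheet would place named HIV-study consents inside the facility.
3. Have staff record on the coded interview form that signed consent was obtained. Proof of consent then survives the shredding of the sheet.
4. Correct the sentences on the only linking record and on the absence of personal identifiers so that they match, and say how long signed forms are kept.

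The cost is a few sentences, a filing rule and one tick box, with no extra staff or data. There is one small downside: once the sheet is shredded, a particular signed form can no longer be matched to a particular coded record.
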